## Research questions (RQ)

- (1) To investigate the risk and protective effects on CVD morbidity and mortality associated with various combinations of moderate alcohol consumption and binge drinking. We will here also look at risk in the sub-group of patients with pre-existing CVD.
- (2) To investigate if the effects of moderate alcohol consumption and binge drinking on CVD can be explained by or interact with mental distress (depression and/or anxiety).
- (3) To investigate if the effects of moderate alcohol consumption and binge drinking on CVD can be explained by or interact with cognitive ability (IQ), educational level, or other socioeconomic factors.
- (4) First, to investigate how alcohol consumption in family members are related to CVD risk among index individuals. Secondly, to use alcohol consumption among siblings and offspring as instrumental variable to assess the causal effects of alcohol consumption pattern on CVD.
- (5) Using pairs of siblings, monozygotic and dizygotic twins discordant for CVD to estimating the association between moderate alcohol and binge drinking and CVD within families. These results will adjust for early life and family factors.
- (6) To assess familial aggregation of mental distress, alcohol related mortality and CVD morbidity and mortality.

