### **Data sources**

The Cohort of Norway (CONOR) Data from 10 epidemiological studies (n=181,891) from 1994-2003 have been merged into a national database. All the surveys included self-reported health and selected diseases, various risk factors, socio-demographic factors, use of medications and physiological measures such as blood pressure, cholesterol, triglycerides, waist and hip circumference, height and weight.

The Norwegian Twin Registry (NTR) Panel II were born 1915-1960. Questionnaires on alcohol consumption were sent out in 1980 and 1990 and 14 500 responded to one of these. These questionnaires included detailed reports on health and risk factors.

Norwegian Family Based Life course Study Data from all 7,400 000 Norwegian citizens alive between 1960 to 2010 has been linked to family data and several health surveys and registers. Family linkage is available for more than 90 % of those born after 1940. This is linked to several other cardiovascular health surveys in addition to CONOR (in total 730,000) and the Conscript Registry.

Hospital discharges on cardiovascular diseases in Norway (FS-data): Data on all cardiovascular hospitalizations in Norway between 1994 and 2009 has been obtained through patient administrative systems at Norwegian hospitals. This includes coronary heart disease (both myocardial infarction and unstable angina), stroke and atrial fibrillation.

Social security registry (FD-trygd): Data on disability pension, sickness and social security benefits on all Norwegian citizens from 1992 onwards. Diagnosis will be ICD-10: F01-F99 (Mental, behavioral and neurodevelopmental disorders)

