### **Samples (sub-populations)**

#### **RQ 1:**

The CONOR and the NTR will be pooled together and the NTR will be used as a cohort for this purpose. This will include n=47,848 from CONOR and n=8028 individuals from NTR (n=55,876 in total) with complete data on both moderate and binge drinking. Mean year of birth is 1947 in CONOR and 1941 in the NTR sample. More deaths occur in the NTR (n=1453 deaths) compared to CONOR (n=1805 deaths). Number of CVD deaths in the CONOR sample with follow-up until 2010 is 547. Based on the proportion of CVD mortality and all-cause mortality and number of fatal and non-fatal cases in the FS-database, total

number of cases, including both CONOR and the NTR is expected to be 3000 IHD and 3500 cases of stroke.

RQs 2 and 3:

This will include the CONOR and twin populations linked to the FS-data on hospital discharges, the Cause of Death Registry, the Conscript Registry (cognitive ability) and Social Security Registry (mental health problems). Two separate sub-populations of CONOR will be studied: all subjects who responded to items on moderate alcohol consumption (n=162,048) and, nested in this sample, those who responded to items on both moderate and binge drinking (n=47,848). In the first group there are 3774 deaths from CVD. There are in total 9735 acute myocardial infarction and 8926 stroke incident cases from the FS-database in CONOR. For the second group, see RQ1.

RQ 4:

This issue will be analyzed in a linkage between CONOR, cardiovascular health surveys in the Norwegian Family Based Life course study and the FS-data on hospital discharges. There are 116,037 individuals in CONOR with information on parents and siblings. Of these, 109,800 individuals have responded on the moderate alcohol consumption question with 9729 CVD deaths in fathers and 31,050 on the binge drinking question with 1854 CVD deaths occurring after the year of CONOR examination.

RQ 5:

CONOR: There are 48,401 siblings in CONOR with the same mother and father. 1025 of these have by 2010 died (281 CVD). We expect approximately 1400 CVD endpoints in the FS-database. For the second group on siblings, see RQ 1.

RQ 6:

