The Cause of Death Registry: All Norwegians alive in 1990 born after 1940 (n=1,095,000) will be followed up for death from with a main and underlying cause of death being alcohol-related dying in the period 1990-2012 (ICD-10: F10.0-F10.1, F10.3-F10.9, F10.2, K29.2 and K70). In a previous publication, we expect approximately 3500 alcohol-related cases. First degree family members will be followed up for CVD outcomes and mental distress CVD morbidity or mortality (The Cause of Death, FS-data and FD-trygd).

Questionnaire 1980 in NTR: In the NTR there are 5149 complete like-sexed twin pairs (n=10,298 individuals) who responded to the questionnaire on moderate alcohol consumption. 2021 individuals of these have died by 2010, including 810 CVD deaths. Based on the proportion CVD mortality and total mortality in the age group, number of fatal and non-fatal cases, and presuming they are followed up for hospital incidents from 1994, we expect approximately 1700 incident hospital cases of IHD and 1950 cases of cerebrovascular disease in the FS-database.

Questionnaire 1990 in NTR: And in the 1990 questionnaire there are 2138 complete twin pairs (n=4276 individuals) who have responded to the alcohol questionnaire in 1990 with information on both moderate and binge consumption. 626 of these individuals have died by 2010, 250 CVD deaths. Here we expect approximately 900 incident hospital cases of IHD and 1040 cases of cerebrovascular disease in the FS-database.

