Data analysis: For time to event outcomes such as morbidity and mortality the primary modelling strategy is to use Cox proportion hazard regression models. In RQ 1 the effect of moderate alcohol consumption will be analysed by adjusting for binge drinking and across strata of binge drinking (interaction term will be fitted to formally test if the effect differs). In RQ 2-3 the same strategy will be employed using strata of cognitive ability and mental health. In RQ 4 the aim is to see if using alcohol consumption among family members as instrumental variable will reproduce a protective effect of moderate alcohol consumption as seen in conventional analysis. Using instruments, it will also be possible to estimate the effect sizes and compare the effect and pattern in CONOR participants with that of their sibling. To achieve this, z-scores will be calculated based on units of alcohol consumption reported. For RQ 5, the effects of alcohol consumption will be estimated by comparison between siblings or co-twins ("fixed effect"). This approach effectively matches out all factors shared between siblings that may confound the effect of alcohol on cardiovascular mortality reported in studies of unrelated individuals. The analyses will be conducted in the statistical software STATA. Age, smoking status and number of cigarettes per day in smokers, physical activity, self-reported disease (CVD, diabetes, antihypertensive medication) and psychosocial distress at baseline will be adjusted for as potential confounders. In

familial aggregation analysis, we will estimate to what extent alcohol related mortality co-occur in first degree family members with CVD morbidity and mortality and mental distress by summing up number of family members with any of these traits.

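### In RQ 6, register mental distress covers all of ICD-10 F01-F99, so alcohol-disorder (F10) benefits in relatives count as mental distress

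*Protocol*

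**What the plan says.** - **Register definition** (Protocol, Data sources, social security registry): "Diagnosis will be ICD-10: F01-F99 (Mental, behavioral and neurodevelopmental disorders". No code within the range is excluded, here or elsewhere.
- **Alcohol-related death** (Samples, RQ 6, Cause of Death Registry): "ICD-10: F10.0-F10.1, F10.3-F10.9, F10.2, K29.2 and K70".
- **Follow-up of relatives** (same paragraph): "First degree family members will be followed up for CVD outcomes and mental distress CVD morbidity or mortality (The Cause of Death, FS-data and FD-trygd". The sentence does not match each source to each outcome. However, the FS-data are described as cardiovascular discharges and the Cause of Death Registry holds deaths, so FD-trygd is the source with mental diagnoses in living relatives.
- **RQ 6 aim** (Research questions): "To assess familial aggregation of mental distress, alcohol related mortality and CVD morbidity and mortality". Mental distress and alcohol-related mortality are listed as distinct traits.
- **RQ 6 analysis** (Statistical methods, Data analysis): the estimate is how far "alcohol related mortality co-occur in first degree family members with CVD morbidity and mortality and mental distress".
- **RQ 2** (Research questions): asks whether the alcohol effects "can be explained by or interact with mental distress (depression and/or anxiety". The sample paragraph for RQs 2 and 3 names the "Social Security Registry (mental health problems" among the linked sources.

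**The concern.** The F10 codes appear on both sides of the RQ 6 comparison. They help to define the index death, and they lie inside the range that defines mental distress in the relatives. The protocol itself calls alcoholism heritable (0.52-0.64) and notes that full siblings and parents share half the genes involved (Approaches, hypothesis and choice of method). F10 benefits should therefore be more common among relatives of people who died of alcohol-related causes, whether or not depression or anxiety runs in those families.

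As defined, that excess enters the mental-distress result. A reader would take a positive finding to mean that alcohol death and psychological distress cluster in families, when part or all of it could be alcohol disorder clustering with alcohol disorder. The section on sample size and power considers it highly likely that meaningful aggregation will be detected, so misattribution is a more pressing risk here than a missed effect.

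**Working it through.** **Step 1: compare the code sets.** The alcohol-death set is F10.0-F10.9 (the listed subcodes together cover all of F10), K29.2 and K70. The register set is F01-F99. Their intersection is all of F10; K29.2 and K70 fall outside. With F10 removed from the register set the intersection is empty.

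**Step 2: locate the overlap.** It lies between two people: the death is in the index person and the benefit is in a relative. What matters is the relative's F10 benefit. An index death coded K70 or K29.2 is also alcohol-related by the protocol's definition, so it too can come with an excess of F10 among relatives.

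**Step 3: is there a figure to reproduce?** No. No stated sample size or power figure depends on the F01-F99 definition.

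**Step 4: illustrate the size.** Let s be the F10 share of F01-F99 diagnoses among relatives of non-cases, RR1 the familial relative risk for F10, and RR0 that for all other F codes. None of these is in the protocol; all values are assumptions.

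Apparent RR = (1 - s) × RR0 + s × RR1

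With RR0 = 1.0 (no other aggregation):

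| s | RR1 | Apparent RR |
|---|---|---|
| 2% | 2 | 0.98 + 0.04 = 1.02 |
| 5% | 3 | 0.95 + 0.15 = 1.10 |
| 10% | 5 | 0.90 + 0.50 = 1.40 |

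If other disorders do aggregate, say RR0 = 1.3, the share of the excess that comes from F10 is s(RR1 - 1) / [(1 - s)(RR0 - 1) + s(RR1 - 1)]:

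- s = 2%, RR1 = 2: 0.02 / (0.294 + 0.02) = 6%
- s = 10%, RR1 = 5: 0.40 / (0.27 + 0.40) = 60%

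**Step 5: would a spurious excess be declared significant?** From the protocol: about 3500 alcohol-related deaths among 1,095,000 people (0.32%), so (1,095,000 - 3500) / 3500 = 312 non-cases per case. Assumed: 2-4 relatives per person, register prevalence of 5-10%, and independent relatives. The test is a two-sided 5% comparison of two proportions.

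| Spurious RR | Probability of significance |
|---|---|
| 1.02 | 0.06-0.12 |
| 1.05 | 0.16-0.50 |
| 1.10 | 0.48-0.97 |
| 1.20 | 0.96 or more |

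Correlation within families would lower these somewhat. At the low end the distortion is negligible. From the middle of the range upwards, it could produce a positive RQ 6 result unaided.

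**The case against.** The best defence is that the overlap is limited. It runs across relatives and registers, not within one person. The alcohol-death set has K codes that chapter F does not contain. RQ 6 means to study aggregation of alcohol-related mortality anyway, so familial alcohol disorder is within its scope. The restriction to depression and anxiety is attached to RQ 2, not RQ 6. Every input to the size estimate is assumed.

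All of this stands as a limit on the claim. It does not remove the fault: scope does not justify labelling alcohol disorder as mental distress when the aim lists the two separately. Nor is the code range a detail left to a later plan. The protocol states it, and an analysis plan that followed it would carry the problem forward.

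Four stronger readings are tempting, and the documents do not support them.

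- **That RQ 2 is compromised in the same way.** Alcohol deaths play no part in RQ 2, where the exposure is self-reported drinking and the outcome is CVD. The CONOR mental health index measures symptoms of anxiety and depression, and the RQ 2 power calculation uses the prevalence of mental distress in CONOR (10%). Only a register-based RQ 2 analysis is exposed: there F10 would make the proposed explanatory or modifying factor partly a marker of drinking. That could matter for the twins, because the index is described for CONOR only and the sample paragraph names no mental health source for them other than the register.
- **That F01 (vascular dementia) builds the outcome into the modifier.** That would require benefits granted after CVD onset to be counted, and the protocol does not say they are.
- **That the familial count is itself an artefact of family size.** The protocol estimates co-occurrence "by summing up number of family members with any of these traits", but does not say that the count is analysed without a denominator, adjustment or comparison group. That detail may properly sit in an analysis plan.
- **That RQ 6 merely correlates alcohol disease with itself.** F10 is one part of a wide range, and the mental-distress result would be a mixture.

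**Conclusion.** The point holds for RQ 6. As written, F10 benefits in relatives count as mental distress, so familial clustering of alcohol disorder is partly reported as clustering of alcohol death with mental distress. This follows from the code ranges alone and needs no outside figure.

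Its size does not follow from the protocol. The apparent relative risk of 1.02-1.40 instead of 1.0 rests on assumed F10 shares of 2-10%, assumed familial relative risks of 2-5 for F10, and no aggregation of any other diagnosis. The true distortion could be trivial or could dominate. Under the stated definition the mental-distress result cannot tell the two apart, and that is the reason to change it.

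For RQ 2 the point is secondary and confined to any analysis that uses the register: F01-F99 is wider than the depression and anxiety named in the question.

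**What to change.** 1. **RQ 6:** exclude F10, and preferably all substance-use codes F10-F19, from the register definition of mental distress.
2. **RQ 6:** analyse F10 benefits in first-degree relatives as a separate outcome, so that familial alcohol disorder is still reported under its own name. State that a relative with both an F10 benefit and another qualifying mental diagnosis counts in each outcome.
3. **RQ 2, where the register is used:** apply the same exclusion and restrict the definition to listed depressive and anxiety codes, to match the wording of the question. The CONOR mental health index needs no change.

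This is a change to a code list and to the outcome definitions; it requires no new data source. The downside is fewer register cases of mental distress, more so under the narrower RQ 2 list. Reporting the number of F10 and F10-F19 benefits among relatives would show how much the exclusion removes and replace the assumed share above with an observed one.

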### **Samples (sub-populations)**

#### **RQ 1:**

The CONOR and the NTR will be pooled together and the NTR will be used as a cohort for this purpose. This will include n=47,848 from CONOR and n=8028 individuals from NTR (n=55,876 in total) with complete data on both moderate and binge drinking. Mean year of birth is 1947 in CONOR and 1941 in the NTR sample. More deaths occur in the NTR (n=1453 deaths) compared to CONOR (n=1805 deaths). Number of CVD deaths in the CONOR sample with follow-up until 2010 is 547. Based on the proportion of CVD mortality and all-cause mortality and number of fatal and non-fatal cases in the FS-database, total

number of cases, including both CONOR and the NTR is expected to be 3000 IHD and 3500 cases of stroke.

RQs 2 and 3:

This will include the CONOR and twin populations linked to the FS-data on hospital discharges, the Cause of Death Registry, the Conscript Registry (cognitive ability) and Social Security Registry (mental health problems). Two separate sub-populations of CONOR will be studied: all subjects who responded to items on moderate alcohol consumption (n=162,048) and, nested in this sample, those who responded to items on both moderate and binge drinking (n=47,848). In the first group there are 3774 deaths from CVD. There are in total 9735 acute myocardial infarction and 8926 stroke incident cases from the FS-database in CONOR. For the second group, see RQ1.

RQ 4:

This issue will be analyzed in a linkage between CONOR, cardiovascular health surveys in the Norwegian Family Based Life course study and the FS-data on hospital discharges. There are 116,037 individuals in CONOR with information on parents and siblings. Of these, 109,800 individuals have responded on the moderate alcohol consumption question with 9729 CVD deaths in fathers and 31,050 on the binge drinking question with 1854 CVD deaths occurring after the year of CONOR examination.

RQ 5:

CONOR: There are 48,401 siblings in CONOR with the same mother and father. 1025 of these have by 2010 died (281 CVD). We expect approximately 1400 CVD endpoints in the FS-database. For the second group on siblings, see RQ 1.

RQ 6:

The Cause of Death Registry: All Norwegians alive in 1990 born after 1940 (n=1,095,000) will be followed up for death from with a main and underlying cause of death being alcohol-related dying in the period 1990-2012 (ICD-10: F10.0-F10.1, F10.3-F10.9, F10.2, K29.2 and K70). In a previous publication, we expect approximately 3500 alcohol-related cases. First degree family members will be followed up for CVD outcomes and mental distress CVD morbidity or mortality (The Cause of Death, FS-data and FD-trygd).

Questionnaire 1980 in NTR: In the NTR there are 5149 complete like-sexed twin pairs (n=10,298 individuals) who responded to the questionnaire on moderate alcohol consumption. 2021 individuals of these have died by 2010, including 810 CVD deaths. Based on the proportion CVD mortality and total mortality in the age group, number of fatal and non-fatal cases, and presuming they are followed up for hospital incidents from 1994, we expect approximately 1700 incident hospital cases of IHD and 1950 cases of cerebrovascular disease in the FS-database.

Questionnaire 1990 in NTR: And in the 1990 questionnaire there are 2138 complete twin pairs (n=4276 individuals) who have responded to the alcohol questionnaire in 1990 with information on both moderate and binge consumption. 626 of these individuals have died by 2010, 250 CVD deaths. Here we expect approximately 900 incident hospital cases of IHD and 1040 cases of cerebrovascular disease in the FS-database.

**Main variables (see full description at [FHI webpage](#))**

**Moderate alcohol consumption**

Questions in CONOR:

1) “Approximately, how often have you during the last year consumed alcohol?” Eight response alternatives were recoded into five categories: Never/seldom, once per month, 2-3 per month, about once a week, 2-3 times a week, 4-7 times a week. 2) “When you drink, how many glasses do you usually drink?” 3) “When you drink, do you usually drink beer, wine or liquor?”

Questions in NTR:

1) “Do you drink beer?” 2) “Do you drink wine?” 3) “Do you drink liquor?” For each of these three questions, quantity was assessed by: “Do you drink less than a glass each day, 1-2 glasses each day or more than 2 glasses each day”.

**Binge drinking**

Questions in CONOR:

“Approximately how often during the past 12 months have you consumed alcohol corresponding to at least 5 glasses of liquor in 24 hours?”

In all 47,848 participants (26,151 men and 21,697 women), and answers varied from zero to 99 times during the last year. Nearly half (46.3%) reported zero, and the frequency was a higher in men than in women.

In NTR:

1990 questionnaire: “Approximately how many times during one year do you drink more than 5 bottles of beer, one bottle of red or white wine or a quarter bottle of liquor?” (Never, 1-4 times a year, 5-10 times a year, once a month, 2-3 times a month, once a week, 2-4 times a week or every day or almost every day?)

Life course socioeconomic position: Highest educational level, household income (yearly updated), Childhood parental occupational class and education, and housing conditions from Censuses 1960 onwards).

Cognitive ability/Intelligence in late adolescence: The Norwegian National Conscript Service examines more than 90% of the male population at age 18-19 years. General ability is a composite score based on 3 speeded subtests. The Arithmetic Test (25 minutes) has 30 items in prose and measures logical reasoning and arithmetic and algebraic ability; it is similar to the arithmetic test in the Wechsler Adult Intelligence Scale (WAIS). The Word Similarities Test (8 minutes) is a multiple-choice test with 54 items, akin to the vocabulary test in WAIS. The Figures Test (20 minutes) has 36 multiple-choice items with 6 or 8 alternatives and is similar to Raven’s Progressive Matrices.

The CONOR mental health index: This consists of summative index including seven questions on mental distress scored 1-4: “Have you, in the course of the last two weeks, felt: Nervous and unsettled? Troubled by anxiety? Secure and calm? Irritable? Happy and optimistic? Sad/depressed? Lonely?” Response categories are “No”, “A little”, “Quite a bit” and “Very”. This index captures a combination of symptoms of anxiety and depression. This index has been validated, has good internal consistency and correlates highly with the total score for Hospital Anxiety and Depression Scale (HADS) ( $r=0.76$ ) and with Hopkins symptom checklist (HSCL-10) ( $r=0.70$ ).

Cardiovascular risk factors: Current smoking, pack years of smoking, Body weight, Height, Waist circumference and Hip circumference, heart rate, systolic and diastolic blood pressures, non-fasting serum total, HDL cholesterol and triglycerides and physical activity.

